### Data management {19}

The General Data Protection Regulation (EU GDPR), the data protection law, the guidelines of the Finnish National Board on Research Integrity (TENK) and the European Federation of Academies of Sciences and Humanities (ALLEA) will be used to guide the research integrity in the implementation of the research. The data protection law as well as the ethical instructions of JYU and the Regional Medical Research Ethics Committee of Wellbeing Services County of Central Finland will be followed in conducting the research and handling subjects in a vulnerable position. In this study, data is not transferred outside the EU/EEA area. The storage of personal data is regulated by legislation and good scientific practice. Personal data is collected only for this study and stored separately from all other data. All data is stored on a secured data server, that has been created for this study by JYU digital services.

Named members of the research group, the professional assessors, and the research therapists will have access to the personal data to the extent that is essential for their duties. A separate data management plan has been prepared, according to which the details of data management are handled during the study.

### Confidentiality {27}

All personal data collected in this study will be carefully handled as stated in a separate data management plan. Confidentiality will be maintained by pseudonymisation of all personal data, that is possible to pseudonymise. Video data or other data that cannot be pseudonymised will be accessed only by the researchers whose duties require working with the data. All other identifiers will be removed after which all data is stored with participant codes, and the code key can be only accessed by the PI.

### Plans for collection, laboratory evaluation and storage of biological specimens for genetic or molecular analysis in this trial/future use {33}

Not applicable as no biological specimens were collected in this trial.

## Statistical methods

### Statistical methods for primary and secondary outcomes {20a}

All statistical tests will be two-tailed with a significance level of 5%, and no adjustments will be made for multiplicity. Primary and secondary outcome measures at baseline, post-intervention, and at the first and second follow-ups will be treated as continuous dependent variables.

For the IIMT group, which also serves as the waiting-list control, we will assess clinical improvement by comparing their progress during the intervention period with that observed during the waiting period prior to treatment. Specifically, we will perform paired samples t-tests for each outcome measure, comparing the change from baseline 2 (6 weeks; pre-intervention) to post-intervention (12 weeks) against the change from baseline 1 (0 weeks; no intervention) to baseline 2 (6 weeks). Prior to analysis, we will assess the normality of the difference scores to ensure the assumptions of the t-test are met. This comparison will help isolate the treatment effect from natural fluctuations over time.

Since the participants are randomised either to the waiting list plus plain IIMT group or to one of the other three arms (B, C, and D), comparisons between plain IIMT and the waiting list are based on within-subject analyses rather than fully randomised group contrasts. No direct comparisons between the waiting list group and arms B, C, and D will be performed.

To evaluate the effects of VAT and ML on these outcomes, repeated-measures linear mixed-effects models will be applied [50]. A key advantage of this design is its ability to retain participants with missing data, ensuring that all participants contribute to the analysis. Additionally, they can account for baseline group differences, to avoid overestimating the effect size of treatment. VAT and ML will be included as fixed effects, with a random intercept for each participant to account for the dependency of repeated measurements. To control for baseline differences across conditions, treatment terms will be omitted from the model, allowing the effects of VAT and ML to be estimated through their interactions with time. As an exploratory analysis, the models will be extended to include a VAT × ML interaction term to examine potential synergistic effects between the two interventions.

In addition to evaluating treatment effects post-intervention and at follow-up time points, we will calculate an overall treatment effect over time (denoted as *B*). This will represent the raw mean difference associated with the presence versus absence of each factor. *B* will be derived by summing the regression coefficients corresponding to each condition across all time points [28]. To estimate effect sizes for each outcome, the overall treatment effect over time will be divided by the baseline standard deviation of the respective measure across all participants.

For each participant, a dichotomous treatment response variable will be calculated, defined as a reduction of at least 50% in CORE-OM scores between the baseline and post-intervention assessments. Fisher’s exact test and odds ratios will be calculated separately for VAT and ML. For statistically significant effects, clinical significance will be assessed by calculating the risk difference and the number needed to treat (NNT).

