### Plans to promote participant retention and complete follow-up {18b}

The participants’ eligibility and ability to commit to the study is assessed at screening to ensure the fit to the protocol. The intervention is designed to meet the needs of the target group thus promoting participant retention and completing the intervention and the whole study. Participants are also encouraged to complete the study. The study will be implemented with high quality at all phases from recruitment to the last follow-up. All testing timepoints will be completed by the same assessor to ensure assessment coherence, and also to enhance participant retention. The participants can have information about their condition at all timepoints which will also promote their commitment to the study. No data will be collected after discontinuance of the study, however, all previously collected data will be included in the analysis.

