### Methods in analysis to handle protocol non-adherence and any statistical methods to handle missing data {20c}

An intention-to-treat (ITT) approach will be employed, incorporating all available data regardless of whether the treatment was received as intended. Participants who discontinue the study before completing the intervention will be classified as dropouts.

For dichotomous variables (e.g., early study termination, treatment response), missing data will be imputed using a conservative approach in which participants who leave the study early will be assumed to have experienced a negative outcome (i.e., dropout or no response).

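### The waiting-list comparison drops any arm A participant who misses one of three visits, which sits badly with the plan to use all collected data

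*Protocol article*

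**What the plan says.** All references are to the protocol article.

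- **Test.** For the group that waits and then receives plain IIMT, section {20a} states: "we will perform paired samples t-tests for each outcome measure". The two members of each pair are the change from baseline 2 to post-intervention and the change from baseline 1 to baseline 2.
- **Data to be used.** Section {18b} states: "No data will be collected after discontinuance of the study, however, all previously collected data will be included in the analysis". Section {20c} states: "An intention-to-treat (ITT) approach will be employed, incorporating all available data regardless of whether the treatment was received as intended".
- **Missing data.** In {20a}, for the mixed models of VAT and ML only: "A key advantage of this design is its ability to retain participants with missing data, ensuring that all participants contribute to the analysis". In {20c}: "For dichotomous variables (e.g., early study termination, treatment response), missing data will be imputed using a conservative approach". Section {20b} adds last observation carried forward (LOCF) as a sensitivity analysis for the primary outcome. No main-analysis rule is given for a missing continuous score in the paired test.
- **Role of the test.** Section {20a} rules out direct comparison of the waiting list with arms B, C and D.

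**The concern.** A participant who completes baseline 1 and baseline 2 and then leaves has given two scores. Sections {18b} and {20c} suggest that those scores will be analysed, but the test named in {20a} cannot use them.

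This matters because, under {20a}, the paired test is the only planned comparison of IIMT with no IIMT, and it rests on about 50 people. Whether someone stays after six weeks of waiting may plausibly depend on how they changed during those weeks, and that change is one of the two halves of the contrast. Selection on it therefore goes straight into the estimate. If improvers leave, therapy looks better than it is. If those who worsen leave, it looks worse. The direction cannot be known in advance, so the bias cannot be called conservative.

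**Working it through.** **Inputs from the document.** Arm A has 50 participants and the intra-participant correlation is ρ = 0.6 (section {14}, where ρ is stated for the mixed model). Tests are two-sided at 5% ({20a}). No dropout rate is given.

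**Assumptions.** Equal variances with correlation 0.6 between all visits; a true contrast of -0.50 SD (negative favours IIMT); probability of a missing post score logistic in the waiting-period change, slope 1 per SD; loss of 5%, 12% or 21%.

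**The plan's own figure.** Section {14} gives this test power 0.9 at d = 0.23. A paired t-test with n = 50 and a standardised difference of 0.23 has power 0.358. The figure 0.9 is met with n = 200 (0.899), or nearly met with n = 50 and a standardised difference of 0.46 (0.890). That is a separate matter, and the present point does not rest on it.

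**Step 1: what the test needs.** Let W = baseline 2 − baseline 1 and T = post − baseline 2. The paired difference is

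D = T − W = post − 2 × baseline 2 + baseline 1.

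If any of the three scores is missing, D is undefined.

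**Step 2: how selection on W enters D.** In units of the outcome SD:

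- Var(W) = 2(1 − 0.6) = 0.8
- Cov(T, W) = 0.6 − 0.6 − 1 + 0.6 = −0.4
- Cov(D, W) = −0.4 − 0.8 = −1.2
- slope of D on W = −1.2 / 0.8 = −1.5

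So a shift of 0.10 SD in the completers' mean waiting change moves the estimate by 0.15 SD.

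**Step 3: size when the wait is completed and the post score is missing (simulation).**

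| Lost | Paired test, improvers leave | Paired test, worseners leave | Likelihood, all scores |
|---|---|---|---|
| 5% | about -0.57 | about -0.44 | -0.50 |
| 12% | about -0.65 | about -0.35 | -0.50 |
| 21% | about -0.75 | about -0.25 | -0.50 |

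Repeat runs agree to within 0.02. With a slope of 0.3 the bias is under 0.1 SD; at 12% loss the paired test gives about -0.55 when improvers leave.

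For scale, Var(D) = 6 − 6 × 0.6 = 2.4. At 12% loss n = 44 and the standard error is √(2.4/44) = 0.23, so a bias of 0.15 is about two thirds of a standard error.

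**Step 4: loss unrelated to outcome.** With 18% lost n = 41, and √(2.4/41) = 0.24. The likelihood estimate has an SD of about 0.23. Neither is biased, and the gain in precision is modest.

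**Step 5: people who leave during the wait.** Here baseline 2 and post are both missing. At 12% loss the paired test gives about -0.65 or -0.35, and likelihood gives about -0.64 or -0.37. Loss now depends on a change that was never observed, and baseline 1 alone says little about it. The model removes almost none of this bias.

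**The case against.** **The {20c} sentence is an adherence clause.** It can be read as saying only that people are analysed as randomised, not that every test must use incomplete cases. That is fair, and a reader who infers a flat contradiction with intention-to-treat goes further than the text. Section {18b} is the closer promise. It is partly kept, because arm A is the cell with neither VAT nor ML and so enters the mixed models, which retain incomplete participants. What stands is that the waiting-list test itself cannot use those data.

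**LOCF is already planned.** It is a sensitivity analysis, covers the primary outcome only, and is not tied to this test. Nor is it neutral here: carrying baseline 2 forward sets the therapy-period change to zero. With 18% unrelated loss and no average change while waiting, it gives 0.82 × (-0.50) = -0.41.

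**The size depends on assumed inputs.** This stands. The slope of 1 has no source in the document, and the Discussion reports low dropout in the earlier trials, although it also notes that this trial has broader inclusion criteria.

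**A SAP may settle it.** It may add a rule for incomplete pairs. But the article names a specific test, and that test as named does not fit the article's own statement on data use.

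**A model is no complete cure.** This also stands. A reader might infer that likelihood estimation makes the comparison unbiased whatever the reason for loss. Step 5 shows otherwise. Nor does it supply a concurrent control, a limitation that {20a} acknowledges.

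**Conclusion.** The point holds in a limited form. The named test excludes any arm A participant missing one of three visits, and this sits badly with {18b} and, less directly, with {20c}. For people who finish the wait but miss the post visit, the bias is about 0.06 to 0.07 SD at 5% loss, 0.15 SD at 12% and 0.25 SD at 21%, in either direction, under the strong assumed slope. It is under 0.1 SD with a slope of 0.3. If loss is as low as in the earlier trials, the effect is small.

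The likelihood result of -0.50 assumes that loss depends only on observed scores. The VAT and ML mixed models are not affected. This is a worthwhile improvement at almost no cost, and does not by itself invalidate the comparison.

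**What to change.** In section {20a}, make the main arm A analysis a repeated-measures model:

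- visits baseline 1, baseline 2 and post as categorical time, with every observed score included;
- unstructured covariance, fitted by REML;
- test of the contrast post − 2 × baseline 2 + baseline 1.

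Keep the paired t-test as a check. With complete data the estimate and standard error agree, and with Satterthwaite or Kenward–Roger degrees of freedom so does the test.

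State in the same place that the model does not correct for people who leave before baseline 2, and report their number and baseline 1 scores. State also that the comparison remains within-subject and uncontrolled.

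The cost is a few sentences and a few lines of code, with no new data. The Trial status section expects recruitment to run to the end of December 2028, so the change can be made well before analysis.

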## Objectives {7}

The aim of the study is to focus on depression and anxiety symptoms of individuals of working age and to expand the scope to cover exhaustion as well. This RCT’s intervention is targeted at adult individuals who are in employment, in their studies, temporarily unemployed, on short-term sick leave or rehabilitation allowance and have one or various of the following disorders or conditions: depression, anxiety, work-related stress or exhaustion.

Objective 1: To examine whether IIMT, offered in four different modifications, improves the participants’ condition relative to the control/TAU (Treatment as usual) group. We also aim to find out whether any of the modifications of the IIMT are more effective than plain IIMT.

Objective 2: To understand whether certain musical responsiveness or personality profile explains a client’s improvement in music therapy.

Objective 3: To increase the understanding of the dynamics of therapeutic change by IIMT in its original form and with selected modifications.

Objective 4: To increase the understanding of the essence, mechanisms and trajectories of work-related stress and burnout and their relationship to depression and anxiety.

Hypothesis 1: All the experiment groups (ML + IIMT, VAT + IIMT, VAT + ML + IIMT) improve significantly relative to the control/TAU group.

Hypothesis 2: ML + IIMT group improves significantly better than the IIMT only group.

Hypothesis 3: VAT + IIMT group improves significantly better than the IIMT only group.

Hypothesis 4: VAT + ML + IIMT group improves significantly better than ML + IIMT, and VAT + IIMT groups.

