## Trial design {8}

The study is a randomised 2 × 2 factorial trial, using four conditions: IIMT, IIMT with an additional component of music listening (ML), IIMT with an additional component of vibroacoustic treatment (VAT), and IIMT with the additional elements of both ML and VAT. A superiority design is adopted with the aim of testing whether the intervention, in different conditions, demonstrates statistically and clinically superior outcomes compared with the comparator.

All sessions regardless of the condition will begin with a preparing exercise called Resonance Frequency Breathing (RFB) [24]. There will be a waiting-list control group to whom the plain IIMT will be offered after six weeks of baseline measurements, allowing a within-subject comparison between baseline and treatment conditions. Each group is offered a therapy process consisting of 12 sessions, conducted twice a week for 60 min each.

Outcomes will be measured before and after the start of the therapy and at two follow up points, 6 months and 12 months after the start of the therapy. For Condition A there will be additional baseline 2 measurements before the start of the therapy (see Fig. 1).

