#### Participant timeline {13}

There are overall four to five testing timepoints in this study: during the recruitment of the participants (baseline), 6 weeks after the beginning of the intervention (post-intervention), 6 months after the beginning of the intervention (first follow-up) and 12 months after the beginning of the intervention (second follow-up). The waiting-list control group will have an additional testing timepoint (baseline 2) at 6 weeks after the initial baseline tests before starting the therapy. This will also act as a new baseline for the intervention.

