#### Sample size {14}

We will recruit 200 working-age adults (18–65 years of age) suffering from one or several of the following disorders: depression (ICD-10: F32 or F33), anxiety (ICD-10: F41), or exhaustion. The sample of participants will be randomised into four groups (50 + 50 + 50 + 50) of which two groups (*n* = 100) will receive vibroacoustic treatment (VAT) and two groups (*n* = 100) not whereas two groups (*n* = 100) will receive music listening (ML) and two groups (*n* = 100) not (see Table 2).

**Table 2 Tab2:** Factorial design

	VAT yes	VAT no	
ML yes	50	50	*n* = 100
ML no	50	50	*n* = 100
	*n* = 100	*n* = 100	

For each condition, the selected sample size provided a statistical power of 0.985 for detecting a medium standardised effect size of Cohen’s d = 0.5 in a mixed-model analysis [47], with a 2-tailed significance level of *p* < 0.05 and intra-participant correlation of ρ = 0.6. For the comparison between IIMT only vs waiting-list control, the selected sample size provided statistical power of 0.9 for detecting a medium effect size (d = 0.23) in a repeated measures t-test, with a 2-tailed significance level of *p* < 0.05. These high-power levels ensure a robust detection of clinically meaningful effects, even after accounting for potential participant dropouts, while reducing the likelihood of Type II errors. Also, the selected sample sizes also retain adequate power (> 0.8) to detect smaller effects (e.g., d = 0.2), thus providing sensitivity to subtle group differences.

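### The neither-factor cell is a six-week wait followed by IIMT, not concurrent plain IIMT, so any effect of the wait enters both main effects by half and the VAT × ML interaction in full

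*Protocol article*

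**What the plan says.** Trial design {8} opens with "The study is a randomised 2 × 2 factorial trial, using four conditions: IIMT, IIMT with an additional component of music listening (ML"), followed by the VAT cell and the cell with both. Objectives {7} takes plain IIMT as the comparator for each component: "Hypothesis 2: ML + IIMT group improves significantly better than the IIMT only group". Hypothesis 3 says the same for VAT.

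There is no separate arm that starts plain IIMT at once. Explanation for the choice of comparators {6b} makes Condition A the waiting-list group, treated after six weeks. Participant timeline {13} adds: "The waiting-list control group will have an additional testing timepoint (baseline 2) at 6 weeks after the initial baseline tests before starting the therapy". It treats that visit as A's fresh pre-treatment baseline and counts all later visits from the start of therapy. Statistical methods {20a} puts A's post-test at week 12 and describes the randomisation thus: "Since the participants are randomised either to the waiting list plus plain IIMT group or to one of the other three arms (B, C, and" […]. It concludes that IIMT against waiting list is a within-subject comparison, and rules out any head-to-head comparison of the waiting-list group with B, C and D.

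The same section estimates VAT and ML from factor-by-time terms in a mixed model with a common baseline mean. The VAT × ML term is added only as an exploratory extension, to look for synergy. On error control it says: "All statistical tests will be two-tailed with a significance level of 5%, and no adjustments will be made for multiplicity".

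**The concern.** In a 2 × 2 design each main effect is credible because the cells differ only in the two factors. Here a third factor, the wait, is present in exactly one cell, the one with neither VAT nor ML. Condition A is half of the 'no' side of both margins, so the wait enters both main effects. It enters the interaction contrast D − B − C + A undiluted. No covariate can separate it, because nobody with VAT or ML waits and everybody without either does.

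At stake is what a VAT or ML result means. If six extra weeks of natural recovery help A, true component effects are diluted and the interaction is pushed towards apparent synergy. If waiting leaves A worse, components that do nothing may look useful. The sensitivity analyses in section {20b} (LOCF and treatment as received) do not bear on this.

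**Working it through.** **Inputs from the protocol.** 50 per cell and 100 v 100 per margin (Sample size {14}, Table 2); "detecting a medium standardised effect size of Cohen’s d = 0.5 in a mixed-model analysis"; "intra-participant correlation of ρ = 0.6"; "the selected sample size provided a statistical power of 0.985"; two-sided 5%. The shift s is not in the documents. It is assumed here at 0.2 and 0.3 baseline SD, in either direction.

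**1. Reproduce the stated power.** The variance of the mean of three post-baseline visits at ρ = 0.6 is (1 + 2 × 0.6)/3 = 0.733. For 100 v 100, SE = √(2 × 0.733/100) = 0.121. At d = 0.5 the ratio is 0.5/0.121 = 4.13, and power is 0.985 (0.984 with the t distribution). This matches.

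**2. Where the shift goes.** Score improvement as positive and let A improve by an extra s.
- VAT margin: (C + D)/2 − (A + B)/2 moves by −s/2.
- ML margin: (B + D)/2 − (A + C)/2 moves by −s/2.
- B − A and C − A, which are Hypotheses 2 and 3 as worded, move by −s.
- Interaction: D − B − C + A moves by +s.
- D − B and D − C do not move.

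**3. Does the choice of baseline remove it?** Let g1 and g2 be natural change in weeks 0–6 and 6–12, with no lasting effect of waiting itself. At post-test B–D carry g1 and A carries g1 + g2.
- Baseline 1 for A: s = g2, which is zero only if nothing changes after week 6.
- Baseline 2 for A in the planned common-baseline model: s = g2 − 0.6 × g1, which is zero only if the two happen to offset.
- Example g1 = g2 = 0.2 SD: baseline 1 moves each margin by 0.10 and the interaction by 0.20; baseline 2 moves them by 0.04 and 0.08.
- Example g1 = 0.2, g2 = 0: baseline 1 gives zero; baseline 2 gives 0.06 and 0.12 in the opposite direction.

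**4. Consequence, on the basis of step 1.** A shift at all three visits moves the margin by s/2. A shift at post-test only moves the three-visit mean by s/3, and so the margin by s/6.

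| s (SD) | Duration | Margin shift | Rejection with no VAT/ML effect (A worse) | Power at d = 0.5 (A better) |
|---|---|---|---|---|
| 0.2 | all visits | 0.100 | 13% | 0.91 |
| 0.3 | all visits | 0.150 | 23–24% | 0.82 |
| 0.2 | post only | 0.033 | 5.9% | 0.97 |
| 0.3 | post only | 0.050 | 7.0% | 0.96 |

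The interaction has SE √(4 × 0.733/50) = 0.242, twice that of the margin, and moves by twice as much, so its false rejection rates are the same. If the common baseline reduces the variance to 0.733 − 0.36 = 0.373, a lasting shift gives false rejection of 21% and 41%, with power of 0.996 and 0.98. A post-only shift gives false rejection of 6.7% and 8.9%.

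**5. Contrasts free of A.** For 50 v 50, SE = √(2 × 0.733/50) = 0.171, which is 0.171/0.121 = 1.4 times that of the margin. Power at d = 0.5 is 0.82 (t) or 0.83 (normal).

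**The case against.** The wait is openly described in several sections, and timing visits from the start of therapy in every arm is defensible. The six-week lag is nominal, since B–D start with the next available therapist (section {16c}). The interaction is already labelled exploratory. The paired t-test uses A's change during the wait, so the plan does collect some information on it. All of this stands. However, change during the wait does not show what waiting leaves behind at later visits, and Objectives {7} still calls the comparator IIMT only.

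The strongest objection concerns size. A reader might infer that the main-effect tests run at 13% to 24% error. The documents do not support that: it needs an assumed shift, of one sign, lasting through 12 months. Six extra weeks may matter at week 12 against week 6 and much less a year on, and the post-only rows are just as admissible. A reader might also infer that bias is certain whichever baseline is used. Step 3 shows only that neither baseline guarantees protection.

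Two cautions also apply to the remedy. In the planned additive model D − B and D − C are the VAT and ML coefficients themselves, so they still contain A. And (D − B) minus the VAT margin equals half of D − B − C + A, so requiring the two to agree would be a low-powered interaction test that could veto true effects.

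**Conclusion.** The concern holds as a matter of structure. The only plain-IIMT cell is a six-week wait followed by IIMT, and any resulting shift s biases each main effect by s/2 and biases B−A, C−A and the interaction by s. No planned analysis isolates it, and the 50% CORE-OM response comparison by VAT and ML inherits it. The size and sign of s are unknown. Under assumed shifts of 0.2 to 0.3 SD, false rejection of a main effect runs from about 6% (post-test only) to 24% (all visits), or power falls from 0.985 to between 0.97 and 0.82. These figures rest on ρ = 0.6, the mean of three visits and no dropout. The bias is zero with baseline 1 if natural change stops at week 6 and waiting leaves no trace; the protocol relies on an assumption of this kind without stating it. This does not invalidate the factorial analysis. It calls for a stated assumption, a sensitivity analysis and restraint over the interaction.

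**What to change.** - In Objectives {7} and Statistical methods {20a}, call the comparator 'six-week wait then IIMT', and state that the factor margins assume the wait has no lasting effect.
- For CORE-OM, prespecify as a sensitivity analysis D − B (VAT given ML) and D − C (ML given VAT), estimated from the model that includes VAT × ML × time, not from the additive model. Hypothesis 4 already names these comparisons.
- Report them with confidence intervals beside the margins, and interpret the margins cautiously where they differ, without a veto rule.
- State that the exploratory VAT × ML interaction cannot be separated from the effect of the wait and will not be read as synergy.

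The cost is wording and two contrasts from a model that is already planned; no new data are needed. Recruitment is expected to run to the end of 2028, so this can be fixed before the final data. The drawbacks are intervals about 1.4 times wider, and that a difference from the margins may reflect either the wait or a true interaction.

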## Interventions

### Explanation for the choice of comparators {6b}

The Condition A serves as a waiting-list control group, and they receive their intervention after a 6-week waiting period. This group will serve as the comparator for the primary intervention. Throughout the study all participants in all groups will receive regular healthcare (treatment as usual).

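### Hypothesis 1 (arms B, C and D against control/TAU) has no analysis: the statistical section rules out the randomised comparison it needs, although the data are already scheduled

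*Protocol article*

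**What the plan says.** Objectives {7}: Objective 1 asks whether IIMT in its modifications "improves the participants’ condition relative to the control/TAU (Treatment as usual) group". Hypothesis 1 is specific about the arms: "All the experiment groups (ML + IIMT, VAT + IIMT, VAT + ML + IIMT) improve significantly relative to the control/TAU group".

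Explanation for the choice of comparators {6b}: Condition A is the waiting-list control, and TAU is not a separate arm: "Throughout the study all participants in all groups will receive regular healthcare (treatment as usual"). The control/TAU group of Hypothesis 1 can therefore only be Condition A while it waits.

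Statistical methods {20a}: "the participants are randomised either to the waiting list plus plain IIMT group or to one of the other three arms (B, C, and D"), and for that reason "comparisons between plain IIMT and the waiting list are based on within-subject analyses rather than fully randomised group contrasts". The next sentence is the prohibition: "No direct comparisons between the waiting list group and arms B, C, and D will be performed".

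Two sets of analyses are kept. One is a paired t-test within Condition A, comparing change during therapy with change during the wait. The other is mixed models, with Fisher's exact tests for response, for the presence or absence of VAT and ML.

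Participant timeline {13}: Condition A has an "additional testing timepoint (baseline 2) at 6 weeks after the initial baseline tests before starting the therapy". B, C and D have their post-intervention visit six weeks after therapy begins. Section {18a} says that every outcome measure is completed at every timepoint.

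**The concern.** A confirmatory hypothesis should map to an analysis. Here the first hypothesis needs a contrast that the analysis section excludes, and the stated reason does not cover the case.

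Two things are at stake. First, if the trial later reports that B, C or D beat the control, the claim will contradict the protocol's own statement and count as unplanned. Second, the randomisation gives an unconfounded comparison of each modified package with waiting plus usual care at about six weeks, and the plan discards it. What is left for treatment against no treatment is a sequential before/after contrast in the 50 people of Condition A, and it concerns plain IIMT only.

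**Working it through.** **Step 1. Does any planned analysis test Hypothesis 1?**

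| Planned analysis | Arms used | Contrast | Tests B, C, D v waiting? |
|---|---|---|---|
| Paired t-test {20a} | A only | change in therapy v change in wait | No |
| Mixed models {20a} | A (treated), B, C, D | VAT yes/no, ML yes/no | No: reference is treated plain IIMT |
| Fisher's exact test, odds ratio {20a} | as above | VAT yes/no, ML yes/no | No |
| Adjusted and sensitivity analyses {20b} | as above | same effects | No |

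**Step 2. Does the stated reason justify the exclusion?** Everyone who receives plain IIMT has first waited, so plain IIMT against waiting is within-subject. That is correct. B, C and D contain different people from A, and section {20a} itself says that allocation between them is randomised. The reason does not reach that contrast.

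**Step 3. Are the data there?** A is measured untreated six weeks after baseline 1. B, C and D are measured six weeks after therapy starts. All outcomes are taken at both visits.

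**Step 4. The protocol's own power figure.** Inputs from Sample size {14}: 50 per arm, d = 0.5, ρ = 0.6, two-sided 5%. Taking the mean of three post-baseline measurements, SD = √((1 + 2 × 0.6)/3) = √(2.2/3) = 0.856. With 100 against 100, SE = 0.856 × √(2/100) = 0.1211, and 0.5/0.1211 = 4.13. Power = Φ(4.13 − 1.96) = 0.985, which reproduces the stated 0.985. The protocol does not give its formula, and some other set-ups come within two percentage points. On this reading the figure belongs to the factorial margins, not to Hypothesis 1, for which no power is stated.

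**Step 5. Power of the excluded contrast**, one visit at about week 6, adjusted for baseline 1, normal approximation. Residual SD = √(1 − 0.6²) = 0.8.

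- One arm against A, 50 v 50: SE = 0.8 × √(2/50) = 0.160; 0.5/0.160 = 3.125; power = Φ(3.125 − 1.96) = 0.88.
- All three arms significant, allowing for the shared control: about 0.74. With s = 0.8/√50 and c = 1.96 × 0.160, this is the average, over the error in A's mean (x·s, x standard normal), of [1 − Φ((c − 0.5 + x·s)/s)]³.
- Pooled B + C + D against A, 150 v 50: SE = 0.8 × √(1/150 + 1/50) = 0.131; 0.5/0.131 = 3.83; power 0.97.

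The protocol gives no dropout rate, so a range is assumed:

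| Assumed dropout | n per arm | Power per arm | Power, all three |
|---|---|---|---|
| 0% | 50 | 0.88 | 0.74 |
| 10% | 45 | 0.84 | 0.68 |
| 20% | 40 | 0.80 | 0.61 |

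Without baseline adjustment, power per arm at 50 v 50 is 0.71 on week-6 scores and 0.80 on change scores.

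**Step 6. The test that is kept.** The within-A quantity is (post − baseline 2) − (baseline 2 − baseline 1) = post − 2 × baseline 2 + baseline 1. With equal correlations its variance is (1 + 4 + 1)(1 − 0.6) = 2.4, so the SD is 1.55. With n = 50 and a raw effect of 0.5 SD, 0.5/1.55 = 0.323, and the paired t-test has power of about 0.61. This concerns plain IIMT, so it is not a like-for-like rival of the figures in Step 5.

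**The case against.** The strongest defence is that the exclusion is deliberate. Trial design {8} describes a 2 × 2 factorial trial with a within-subject comparison for the waiting-list group, and the VAT and ML effects keep a randomised analysis. On that view the fault lies in Hypothesis 1, and withdrawing it would also settle the matter. This stands: either route is acceptable, but the text cannot keep both statements.

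Several stronger readings are tempting and are not supported.

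- *Section {6b} also contradicts the analysis.* It says of Condition A: "This group will serve as the comparator for the primary intervention". But section {11a} calls IIMT itself the primary intervention, so the sentence fits the within-A comparison. The firm conflict is between {7} and {20a}.
- *The power for Hypothesis 1 is 0.97.* That figure is for the pooled contrast, which can be significant while one arm shows nothing. The hypothesis is about all the groups, so 0.88 per arm and 0.74 jointly are the relevant figures.
- *A 0.97 test is being replaced by a 0.61 test.* The two address different questions: modified packages against waiting, and plain IIMT against waiting. The randomised contrast cannot replace the within-A analysis, which is the only planned evidence on the latter.
- *Regression to the mean makes the within-A test wrong by a known amount.* Entry is by MADRS, HADS-A or KEDS, not CORE-OM, so the effect reaches the primary outcome only through correlation with those scales. The documents give no figure for its size, and section {20a} claims only that the comparison will help to separate the treatment effect from natural change.

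One practical objection has weight. Six weeks runs from baseline testing in A but from therapy start in B, C and D, and section {16c} passes each participant to the next available therapist, with no stated limit on the delay. Any delay gives B, C and D more time for natural recovery and so favours treatment. Recording visit dates does not by itself remove this.

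**Conclusion.** The point holds as a contradiction that must be resolved. Hypothesis 1 and the control/TAU part of Objective 1 have no analysis, and the reason given for excluding the comparison applies only to plain IIMT. The excluded contrast is randomised and uses scheduled visits. Its power at d = 0.5 is about 0.88 per arm and 0.74 for all three arms, falling to about 0.80 and 0.61 at 20% dropout. These figures rest on the protocol's ρ = 0.6 and 50 per arm, on baseline adjustment, the same true effect in each arm, unadjusted two-sided 5% tests and an assumed dropout rate.

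A reader might infer that the trial has no randomised analysis at all, or that the within-A comparison is worthless. Neither follows. The factorial effects are randomised. The within-A test is usable as supportive evidence on plain IIMT, but its two periods are sequential, so early recovery or regression to the mean of unknown size can bias it. The randomised contrast supports a claim at about week 6 only, because A is treated afterwards.

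**What to change.** Delete the prohibition in {20a} and add:

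1. Hypothesis 1 is tested by three arm-wise contrasts of CORE-OM: B, C and D at post-intervention, each against A at baseline 2, adjusted for baseline 1 or with baseline 1 constrained equal across arms. The pooled 150 v 50 contrast is a secondary summary.
2. The power statement for these contrasts, per arm and for all three together, with the assumed dropout.
3. Actual time since baseline 1 is recorded and allowed for in the analysis, the delay from baseline to first session is reported by arm, and the claim is limited to about week 6.
4. The within-A comparison stays as supportive, non-randomised evidence on plain IIMT.

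If the sponsor does not want the randomised contrast, Hypothesis 1 and the control/TAU part of Objective 1 should be withdrawn.

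The cost is wording and a small amount of modelling, with no new visits. Baseline 2 is now treated as A's new baseline, so this contrast needs its own time coding or a separate model. It also adds three main tests and one summary to a plan without multiplicity adjustment, so the article should say that Hypothesis 1 is met only if all three contrasts are significant. Section {21b} plans no interim analysis and recruitment is expected to run to December 2028, so the change can still be prespecified.
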